## Abstract

**Background:**

The primary aim of this paper is to describe the design of a project evaluating the effects of using a research-based strategy for managing housing adaptations (HAs). The evaluation targets clients’ perspectives in terms of activity, participation, usability, fear of falling, fall incidence, use of mobility devices, and health-related quality of life, and determines the societal effects of HAs in terms of costs. Additional aims of the project are to explore and describe this strategy in relation to experiences and expectations (a) among clients and cohabitants and (b) occupational therapists in ordinary practice.

**Methods/design:**

This study is a quasi-experimental trial applying a multiphase design, combining quantitative and qualitative data. At the experimental sites, the occupational therapists (OTs) apply the intervention, i.e. a standardized research-based strategy for HA case management. At the control site, the occupational therapists are following their regular routine in relation to HA. Three municipalities in south Sweden will be included based on their population, their geographical dispersion, and their similar organizational structures for HA administration. Identical data on outcomes is being collected at all the sites at the same four time points: before the HA and then 3, 6, and 12 months after the HA. The data-collection methods are semi-structured qualitative interviews, observations, clinical assessments, and certificates related to each client’s HA.

Primary outcomes are the usability of the home and the client’s independence in daily activities (ADL). Cross-sectional and longitudinal data analyses will be conducted as well as statistical analyses, health-economic analyses, and qualitative analyses. Qualitative and quantitative data will be sequentially analyzed, and case studies will be developed.

**Discussion:**

The intervention in this study has been developed and tested through many years of research and in collaboration with practitioners. This process includes methodological development and testing research aimed at identifying the most important outcomes and research targeting current HA case-management procedures in Swedish municipalities. When the study is completed, the results will be used for further optimization of the practice strategy for HA, in close collaboration with the data-collecting OTs.

**Trial registration:**

No: NCT01960582.

## Background

The global prevalence of moderate and severe disabilities is estimated at 15% of the general population and at 50% among those aged 60 and up [1]. To a large extent, disabled persons experience problems in daily life owing to physical and social barriers in the environment [1]; therefore, disability can be reduced by adapting the environment [2].

In Sweden, in compliance with the Housing Adaptation Act [3], housing adaptations (HAs) can be provided to people who experience a declining functional capacity to eliminate physical environmental barriers in the home in order to promote independence and safety. HA in this study are defined according to the Swedish law as adaptation of solid features in the home [3], such as removal of thresholds, installation of grab bars or removal of a bath tub and installation of a shower. HA is a publicly funded intervention, administered by a given municipality in response to a client’s application. The full costs of the HA are granted based on needs assessment and certification by a health professional, most often an occupational therapist (OT) employed by the municipality.

When it comes to outcomes of HA, previous research has indicated that HAs improve independence in terms of activity and participation [4–7], reduce difficulty performing activities [8], and improve the usability of the home [4,5]. In this respect, then, the aims of the intervention seem to have been fulfilled. Moreover, falls and the consequences thereof are common, often resulting in injuries, morbidity, and increased health-care costs [9], but research has shown that fall-related disability is positively affected by HA, particularly among people who have a history of falling [6,10]. Thus, it seems that HAs have the potential to counteract injuries in the home and contribute to increased independence.

Although health deteriorates along an ageing and disablement process, disability may be reduced through the effects of HAs. Higher housing standards and more efficient provision of HAs have been shown to contribute to stability in daily activities and health [11,12]. However, the home also has a symbolic meaning for individuals and their cohabitants, who can be negatively affected by changes to its physical design [13]. Very often, clients who implement HAs also use mobility devices (MDs) indoors, outdoors, or both. MDs are prescribed based on the assumption that they reduce falls and improve activity and participation. Consequently, there is a close link between HA and MD, since prescribing an MD very often calls for an HA, and the two are often negotiated in relation to each other in intervention planning. In spite of this, the combined effects of HA and MD on falls and other disability-related outcomes are to a large extent unknown.

There is a sharp contrast between the relevance of HA and the dearth of economic evaluation of these interventions. Few papers have addressed the costs of assistive technology programs [14–16]. So far only one published study reports a full economic analysis of a home-based intervention that included HA [17]. Although this intervention was cost-effective in terms of life years saved [17], it is difficult to isolate the effect of an HA alone. The interventions compared comprised not only HAs but also a number of other activities. In addition, these findings could have limited generalizability in the Scandinavian context given the differences in costs and funding structures between different countries [18].

When it comes to Sweden, which is the setting for this project, the total cost of the approximately 76,000 HAs approved and funded each year is approximately €115.5 million. Two-thirds of the clients are older people with progressively declining health, whereas younger people and adults with considerable functional limitations comprise a non-negligible group of HA recipients [19]. Thus, the group is quite heterogeneous in terms of functional capacity and health, as well as in terms of housing conditions and standards.

In relation to needs assessment and evaluation, a web-based survey targeting Swedish OTs (N =1,679) [20] showed that most HAs were based on unstructured assessments and non-evidence-based methods and that follow-ups were rarely undertaken. Swedish guidelines for management of the HA process are not based on research and are to large extent insufficient. Consequently, there is a need for research-based, structured strategies for HA case management in Swedish municipalities.

### Hypothesis and aims

The hypothesis of this study is that a new intervention strategy for OTs that takes a research-based and structured approach to assessing and evaluating clients who request new HAs can increase the usability of the home; maintain or increase activity, participation, and health-related quality of life, as well as MD use; and decrease fall incidences and the fear of falling (with respect to the standard approach in ordinary practice). An additional hypothesis is that the new intervention strategy will yield health-economic benefits.

The primary aim of this paper is to describe the design of a project evaluating the effects of using a research-based strategy for managing housing adaptations (HAs). The evaluation targets clients’ perspectives in terms of activity, participation, usability, fear of falling, fall incidence, use of mobility devices, and health-related quality of life, and determines the societal effects of HAs in terms of costs. Additional aims of the project are to explore and describe this strategy in relation to experiences and expectations (a) among clients and cohabitants and (b) occupational therapists in ordinary practice.

## Methods & design

### Design of the study

This quasi-experimental trial with a non-equivalent control group uses a before-after design [21]. The study applies a mixed-methods design [22] that combines quantitative and qualitative data. At the experimental sites, OTs apply an intervention that consists of a standardized research-based strategy for HA case management. That is, at the experimental sites, the OTs must change their HA practices, whereas at the control site, the OTs work according to their regular HA routines. The HA process at the experimental and control sites is described in Figure 1. Owing to the nature of the intervention, there is no blinding to study the condition assignment. This applies to the study participants, those administering the interventions, and the assessors.

**Figure 1 Fig1:**
[figure not shown]
**Flow**-**chart of the HA process in the control and intervention municipalities.**

At all the sites, identical data on outcomes are being collected at the same four time points: at T1 (before the HA) and then 3, 6, and 12 months after the HA (T2, T3, and T4, respectively). The data-collection methods are structured interviews, observation, and clinical assessments, as well as examining documents, such as grant proposals, certificates, grant decisions and invoices related to each client’s HA.

Quantitative and qualitative data from surveys, observations, interviews, and certificates will be collected and analyzed separately and combined with case studies, both cross-sectionally and longitudinally. Applying different mixed-methods research designs, data will be merged and combined in order to respond to the different research questions. For the qualitative research the RATS guidelines have been applied [23].

The study has been approved by the Ethical Review Board in Lund, Sweden (Dnr: 2012/566).

### The settings

Three municipalities in south Sweden will be included in this study: two experimental sites and one control site. We selected the municipalities based on the number of their inhabitants, their geographical dispersion, and their similar organizational structures for HA administration. Furthermore, because of the project’s complexity and duration and the effort required (particularly at the experimental sites), it is also necessary that staff members and their leaders (on several organizational levels) express a sincere interest in participating in the study and a readiness to change their practices [24,25].

### Participants

In the intervention and control municipalities, all the OTs who conduct HA needs assessment and certification as part of their ordinary practice are eligible for inclusion in the study. These OTs are the ones who identify potential clients for inclusion in the study.

All the sites have identical inclusion and exclusion criteria in relation to clients. All non-institutionalized persons over 20 years of age who apply for a HA grant via one of the OTs employed by the municipality are systematically considered eligible to participate in the study. Exclusion criteria constitute living in sheltered housing and/or an inability to communicate or follow instructions in Swedish. After a client has contacted an OT in relation to a HA errand, the OT asks the client whether he or she is willing to participate in the study. Participation in the study is completely voluntary and the participants receive oral and written information about the study and are giving their informed consent by signing a paper. Withdrawal or declined participation in the study does not affect further services.

#### Sample size calculation

The power calculation is based on data from a longitudinal study of the HA process [4,5]. Current power estimates are calculated based on primary outcomes: (1) dependence in daily activities, measured by means of the Activities of Daily Living (ADL) Staircase [26] revised version [27]; and (2) usability in the home, measured by the Usability in My Home (UIMH) instrument [28,29].

According to formal calculation, a sample size of 117 people in each municipality is required in order to detect the effect of the intervention with a statistical power equal to 80%. This size is based on an expected improvement of 0.5 in the ADL Staircase score and one of 1.5 on the UIMH score. This calculation is based on the assumption that an HA is effective in both experimental and control municipalities but that the effect is greater at an experimental site.

Given that we expect a drop-out rate of 30% over time in both groups owing to frailty, a total of 170 participants will be recruited at both experimental sites and the same number at the control site. Based on data from previous research, we anticipate that approximately 50% of those will use MDs outdoors or indoors [4,5], thus allowing meaningful sub-group analyses.

For the explorative segment targeting users’ perspectives, 20 clients and 10 cohabitants will be strategically selected for qualitative interviews. The selection will be based on data collection at T1, and the ambition is to make the sample as diverse as possible [30] in terms of sex, age, and MD use. Ideally, 10 in 20 clients should be living alone, whereas the remaining 10 should be cohabiting. The 10 significant others of cohabiting clients will also be invited for individual interviews.

### The intervention

The intervention is the application of a standardized research-based practice strategy for HA case management.

The development of the intervention was directed throughout by the Medical Research Council’s (MRC) guidelines [31], including dividing the process into the following stages: developing, piloting, evaluating, and implementing. The intervention consists of a new practice strategy comprising standardized procedures for the assessment and evaluation of both person- and housing-related aspects. Strategy development was guided by theories and models from medicine and health—namely, the International Classification of Functioning, Disability, and Health (ICF) [2], occupational therapy [32], environmental gerontology [33], and current Swedish legislation governing housing design, HAs [3,34], and MD provision [35]. Given the strong focus on evaluation, as well as the strong relation of the intervention to current policy and legislation in Sweden and to the MRC model, we also apply the theories of practice for guiding programme evaluation that Shadish, Cook, and Leviton [36] have outlined. In order to realize an evaluation that can capture both clinical and economic perspectives, Øvretveit’s [37] work on evaluation of health intervention is combined with health-economic theory and models about the effectiveness, cost, and cost-effectiveness of the intervention [38].

The intervention involves conducting structured assessments with standardized measurements. The variables selected are important as outcomes of HA or are included based on the assumption that they contribute to the structure and focus of the OT assessment. Some variables are included for participant-descriptive purposes. The intervention at experimental sites consists of the following structured components:An extensive training course for OTs covering the standardized research-based practice strategy. The 5-day course extends over 3 or 4 weeks. The research project team is responsible for the course and for training the OTs. The course covers how to conduct a structured assessment; how to use comprehensive and validated instruments in a structured way; and the background, purpose, construction, and basic psychometric properties of each study instrument, along with real-life situation assessments. The training also covers procedures for selecting participants and gaining informed consent, and it addresses ethical issues. The training course includes pilot assessments of the OTs before they begin data collection.OT assessments of physical environmental barriers and housing accessibility prior to HA certification.OT assessment of client outcomes in terms of ADL dependence, need for formal and informal help in the home, and MDs prior to HA certification.Client’s self-administered assessments of home usability, fear of falling, retrospective falls, participation and satisfaction, client goal fulfilment, and health-related quality of life prior to HA certification.Follow-up on client outcomes (i.e., according to OT assessments and self-reports) at home visits that take place 3, 6, and 12 months after HA implementation.

To strengthen data validity and reliability and to facilitate the incorporation of the intervention into ordinary practice, the following operations are planned:Project leaders will arrange regular seminars to increase compliance and adherence to the study protocol. The seminars aim to deepen OTs’ understanding of the intervention components and their competence in assessment and data analysis. One seminar in the early phase is organized as a focus-group interview, followed by additional focus-group meetings after 6 and 12 months.Individual contacts with OTs are undertaken via telephone or workplace visits for support and to clarify any questions that arise.

### The control municipalities

In the control municipalities, the OTs will not receive any specific training; they work according to their regular routines for HA case management. Thus, needs assessment will not necessarily employ instruments, follow-ups will be carried out occasionally (depending on local routines), and each OT will be free to register and manage client records according to the traditional structure used in the municipality. All the clients who meet the inclusion criteria and who have agreed to participate in the study will be contacted by a project administrator (i.e., a trained OT) who collects all data. Since the project administrator will do assessments in the control municipality similar to those the OT conducts at the experimental sites, the control group will receive more attention than usual, but not from a professional involved in the HA or other interventions. That is, the clients and their cohabitants receive the same amount of attention in both municipalities.

### Outcomes and measurements

Primary and secondary outcomes have been identified based on previous research findings, as outlined earlier, as well as based on current Swedish legislation concerning building design and HA.

Table 1 provides an overview of all the outcomes measures and other types of data collected.

**Table 1 Tab1:** **Outcome measures and follow ups**

**Primary outcome**	**Measurements**	**Baseline**	**3 months**	**6 months**	**12 months**
		**(T1)**	**(T2)**	**(T3)**	**(T4)**
Usability of the home	Usability in My Home instrument [28,29].	X	X	X	X
ADL dependence and difficulty	ADL Staircase [26,41].	X	X	X	X
**Secondary outcome**					
Fear of falling	The Short Falls Efficacy Scale-International [42].	X	X	X	X
Fall incidence	Retrospective self-report on falls incidences during the last six months	X	X	X	X
Mobility devices	Self-reported use and need	X	X	X	X
Participation and satisfaction	Self-reported aspects of participation and satisfaction.	X	X	X	X
Health-related quality of life and quality adjusted life years (QUALYs)	EQ-5D-5L [47].	X	X	X	X
Cost	Item on costs for staff, material, travel, administration, etc.	X	X	X	X
Repeated HA	Self-reported question and register data from the municipality		X	X	X
Relocation	Self-reported question		X	X	X
Formal and informal care	Items on formal and informal care, who, and minutes per week, self-reported	X			X

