#### Secondary outcomes

Client levelFear of falling is measured using the short form of the Falls Efficacy Scale-International [42], which consists of seven items (i.e., activities).Falls are targeted based on previous research [43] and measured using structured questions that concern frequency, fall rate, locations, injuries [44], and the frequency of near falls [45].Participation and satisfaction are assessed by means of study-specific questions based on previous research [46] and on the current goals of HA. This includes responding to 8 statements concerning the frequency of and client satisfaction with performance-related participation and togetherness-related participation.Health-related quality of life is measured by means of the EQ-5D-5 L [47]. This is a standardized instrument consisting of a descriptive system targeting mobility, self-care, usual activities, pain/discomfort, and anxiety/depression, in combination with the EQ visual analogue scale.Data on the type of MD and the frequency and location of its use are collected by means of the personal component of the Housing Enabler (HE) instrument [48], as well through questions used in previous research [43].Client goal fulfillment is investigated by means of open questions concerning specific goals and achievements with the HA before and after the intervention to the client and occupational therapist.

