#### Effects on the client level

Statistical analyses will be conducted on the group and sub-group levels, and common descriptive, inferential, and exploratory statistics will be applied. Depending on the characteristics of the variables, parametric and non-parametric statistics will be used, and both variable-based and person-based statistical analysis approaches [51] will be considered. All statistical analyses will be finally decided upon and described in subsequent papers, depending on the specific research questions they target.

Differences between the intervention and control groups in primary and secondary outcomes will be analyzed cross-sectionally at baseline and 3, 6, and 12 months later. Changes over time in outcomes will be calculated by means of a sign test for nominal data, Wilcoxon’s test for ordinal data, and a t-test for interval data. For correlations between single variables, Spearman’s rank correlation will be used, whereas canonical correlations will explore relationships among multivariate combinations of variables [52].

Because the study has a structure in which participants are nested within the municipalities, we will use hierarchical mixed-effects regression models and multi-level modeling approaches to evaluate differences between the intervention and control groups in changes over time in primary outcomes, as measured by the ADL Staircase and UIMH instruments, and in all secondary outcomes. Potential relations between different primary and secondary outcomes will be investigated by means of correlation analyses and Structural Equation Modeling Techniques (SEM). A mixed-linear-effects model will be used to examine the relation between client outcomes and client, as well as environmental characteristics, before and after the HA. The method is a development of regression and ANOVA, allowing a model of “within-subject dependence.” In order to generate knowledge of different groups’ patterns of changes, we will conduct a person-oriented analysis.

Missing data will be imputed following the guidelines for each instrument.

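### The six-month fall recall does not fit the 3-month visit: half of the T2 window lies before the housing adaptation, and the other half is counted again at T3

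*Protocol article*

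**What the plan says.** In the protocol article, the fall incidence row of Table 1 (secondary outcomes) gives one measurement rule, "Retrospective self-report on falls incidences during the last six months", with a mark under T1, T2, T3 and T4. The design section sets the visits "at T1 (before the HA) and then 3, 6, and 12 months after the HA (T2, T3, and T4, respectively").

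The Secondary outcomes section says that falls are "measured using structured questions that concern frequency, fall rate, locations, injuries [44], and the frequency of near falls [45"]. It gives no other recall period for any visit, and neither does the description of the intervention components.

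The hypothesis is that the new strategy can "decrease fall incidences and the fear of falling (with respect to the standard approach in ordinary practice"). Under Effects on the client level, group differences in primary and secondary outcomes "will be analyzed cross-sectionally at baseline and 3, 6, and 12 months later". Mixed-effects and multilevel models are to evaluate group differences "in changes over time in primary outcomes, as measured by the ADL Staircase and UIMH instruments, and in all secondary outcomes". Nothing there restricts the fall analyses to particular visits or adjusts for overlapping recall.

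**The concern.** A fixed six-month look-back suits a visit only if at least six months have passed since the event that starts follow-up, and since the previous visit. T2 fails the first condition and T3 fails the second. The plan states the window and the visit times, so this is not detail left to a fuller document: the two stated rules do not fit together.

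Two planned analyses are affected. The cross-sectional comparison at 3 months would be read as an early effect on falls, although half of the recalled time came before the HA. The longitudinal model would treat T2 and T3 as successive periods although they share three months of events. Fewer falls is part of the stated hypothesis, so the 3-month result is likely to be reported and interpreted.

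**Working it through.** **Inputs.** Recall length W = 6 months at every visit (Table 1). T2, T3 and T4 at months 3, 6 and 12, with the HA at month 0 (design section). The article gives no fall rate, fall effect or power for falls, so there is no figure of its own to reproduce. The rate ratios below are assumptions.

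**Windows.** Each window runs from (visit - W) to the visit.

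| Visit | Window (months) | Share before the HA | Overlap with previous follow-up window |
|---|---|---|---|
| T2 | -3 to +3 | 3/6 = 50% | n/a |
| T3 | 0 to +6 | 0% | months 0 to 3 (3 months) |
| T4 | +6 to +12 | 0% | none |

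The overlap is all of T2's post-HA time and half of the T3 window. These results need no assumption beyond the stated window and visit times.

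**Overlap with baseline.** If T1 takes place g months before the HA, its window ends at -g, and the T1-T2 overlap is max(0, 3 - g): 3, 2, 1 and 0 months for g = 0, 1, 2 and 3. The article does not give g.

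**Dilution at T2.** Assume a constant fall rate in the control group, no group difference before the HA, and a ratio RR after it. The observed ratio at T2 is (3 + 3 × RR)/6 = 0.5 + 0.5 × RR.

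| Assumed RR after the HA | Observed at T2 | Share of log effect kept |
|---|---|---|
| 0.5 | 0.75 | 42% |
| 0.6 | 0.80 | 44% |
| 0.7 | 0.85 | 46% |
| 0.8 | 0.90 | 47% |
| 0.9 | 0.95 | 49% |

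For example, ln(0.85)/ln(0.70) = 0.456.

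**If the groups already differ.** With a ratio D before the HA, the T2 ratio is (3 × D + 3 × RR)/6. With no post-HA effect (RR = 1) and D = 0.9, T2 shows (2.7 + 3)/6 = 0.95, an apparent benefit that precedes the HA. With D = RR = 0.70, T2 shows 0.70 and nothing is diluted. The direction of error therefore depends on D.

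**Change over time.** Months 0 to 3 are in both counts, so T3 minus T2 equals falls in months 3 to 6 minus falls in months -3 to 0. That is a before-after contrast, not a change between two post-HA periods. With RR = 0.70 throughout and D = 1, the model would see 0.85 at T2 and 0.70 at T3, which looks like an effect that grows between 3 and 6 months when it was constant.

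**The case against.** The strongest reply is that the fall data already collected contain a sound answer. T3 covers months 0 to 6 and T4 covers months 6 to 12. Both lie wholly after the HA and they do not overlap, so T3 plus T4 is a valid 12-month count. This stands. A reader might infer that only T4 is usable, that T3 merely repeats T2, or that every follow-up total is wrong. The documents do not support this: T3 repeats only the post-HA half of T2, and no sum of T2, T3 and T4 is planned.

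Second, the hypothesis compares two case-management strategies, not periods before and after the HA. Both groups receive HAs, and the structured assessments at the experimental sites begin before certification. Months before the HA are therefore not necessarily free of the intervention, and the 0.85 figure depends on assuming no group difference in those months. This also stands, and it rules out saying that T2 is always biased toward no effect. It does not rescue T2 as a post-HA outcome: the control group is non-equivalent by design, so an existing difference in falls would be mixed in and could not be separated.

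Third, mixed models allow for within-person dependence, so shared events need not invalidate them. This stands in part. Such models can represent extra correlation, and the T3 and T4 contrasts are not biased by it. They cannot remove pre-HA falls from T2 or make the T2-to-T3 change a comparison of distinct periods.

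Last, falls are one of several secondary outcomes, and the power calculation rests on the ADL Staircase and Usability in My Home. This stands and limits the severity.

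**Conclusion.** The point holds for T2 and for its overlap with T3. As written, the 3-month fall comparison measures three months before and three months after the HA, and months 0 to 3 are counted at both T2 and T3. The 50% share and the 3-month overlap follow directly from the stated window and visit schedule. The size of the distortion does not: a true ratio of 0.70 showing as 0.85 assumes a constant fall rate and no group difference before the HA.

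A reader might infer that the trial's fall evidence as a whole is unsound, or that the main results are at risk. Neither follows. T3 and T4 give clean comparisons and a full 12-month count, and the primary outcomes and sample size are untouched. Severity is moderate: one of three follow-up points of a secondary outcome that is named in the hypothesis.

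**What to change.** Define the follow-up fall outcome as T3 plus T4, covering months 0 to 12. Report the existing six-month T2 count descriptively and keep it out of the between-group effect estimates and the change-over-time models for falls. This takes a line or two of analysis text and no change to forms. The cost is that no 3-month effect on falls is estimated.

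Alternatively, where forms can still be changed, ask at T2 for falls since completion of the HA, and at T3 and T4 for falls since the previous visit. The windows become 0 to 3, 3 to 6 and 6 to 12 months, with no pre-HA time and no overlap, and the T2 ratio then equals the post-HA ratio (0.70 rather than 0.85 in the example). Keep six months at T1 and analyse rates with log recall time as an offset, so that the shorter windows compare with the six-month baseline; raw change in counts would no longer compare like with like. The cost is fewer falls per window at T2 and T3. Data collection is described as under way, so if wording changes midway, the version used for each client and visit must be recorded.
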